### Sample size considerations

Power calculations for sample size were performed in PASS (V.16). They were based on the number of LGs recruited and the number of non-seasonal facilities that agreed to provide display and point-of-sale data used to evaluate the sales outcomes. This included 21 non-seasonal facilities in four LGs in the Intervention group and 14 facilities in four LGs in the Control group (mean n=5 and n=4 sites per LG, respectively). *Primary implementation outcome*: The trial will have 80% power to detect a mean difference between groups of ≥18.8% in the percentage of ‘RED’ drinks displayed at the end of the 3-year trial (intraclass correlation coefficient 0.05, cluster size variation coefficient 0.37, SD=17.8, α=0.05, 2-sided test).^16 30^ This effect size is similar to that observed in the Water in Sport project—an uncontrolled pre-post natural experiment conducted in sports and recreation settings in Victoria, Australia (−18.9% at 18 months).^16 30^
*Primary effectiveness outcome*: With 156 weeks of sales data, the trial will have 80% power to detect a difference of ≥9% between groups in the percentage of ‘RED’ drink weekly drink sales at the end of the 3 year trial, using a generalised estimating equation (GEE) model assuming linear trends^36^ (first-order autoregressive, AR(1) correlation structure, ρ=0.73, SD=13.7). This effect size is smaller than in Water in Sport (−11% at 2 years).^30^ As of December 2024, due to the drop-out of one recruited LG and the withdrawal of some individual facilities in other LGs, the trial involves three LGs in the Intervention group, with a total of 16 non-seasonal facilities, and four LGs in the Control group, with a total of 8 non-seasonal facilities.

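### The 80% power stated for both co-primary outcomes is a design-stage figure; at the facility numbers reported in the same paragraph it is about 61–63%, and the protocol does not restate it

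*Protocol article*

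**What the plan says.** All the relevant text is in the protocol article, Sample size considerations.

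- Basis of the calculation: "This included 21 non-seasonal facilities in four LGs in the Intervention group and 14 facilities in four LGs in the Control group".
- Display (the co-primary measure of implementation): "The trial will have 80% power to detect a mean difference between groups of ≥18.8% in the percentage of ‘RED’ drinks displayed", assessed after 3 years, with these inputs: "intraclass correlation coefficient 0.05, cluster size variation coefficient 0.37, SD=17.8, α=0.05, 2-sided test". The section describes this effect as similar to the −18.9% seen in the Water in Sport project.
- Effectiveness outcome: with 156 weeks of data, "the trial will have 80% power to detect a difference of" at least 9% in weekly RED drink sales, from a GEE model with linear trends, AR(1) correlation 0.73 and SD 13.7. On the benchmark it adds: "This effect size is smaller than in Water in Sport", where the figure was −11%.
- Position in December 2024, after one LG dropped out and some facilities withdrew: three Intervention LGs "with a total of 16 non-seasonal facilities, and four LGs in the Control group, with a total of 8 non-seasonal facilities".

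No revised power or detectable difference follows. The section on limitations covers selection, staff turnover and sustainment, but not loss of precision.

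**The concern.** The power claims are in the future tense ("The trial will have 80% power to detect a mean difference between groups of" 18.8 points or more), but the numbers behind them no longer describe the trial. Between the calculation and December 2024 it lost 11 of 35 facilities, 6 of them from the 14 in Control, and one of the eight LGs.

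These are the co-primary outcomes. If neither shows a difference, a reader who takes the section at face value could conclude that effects of 18.8 and 9 points had been looked for with an 80% chance of detection. At the current size, the chance of missing such effects is nearer 37–39% than 20%, on the plan's own inputs. The two benchmark comparisons reassure in the same way, since they suggest that the trial can detect what the earlier project observed.

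**Working it through.** **Inputs, all from Sample size considerations.** Display: SD 17.8, ICC 0.05, cluster-size CV 0.37, two-sided α 0.05. Sales: SD 13.7, AR(1) ρ 0.73, 156 weeks; two-sided α 0.05 is assumed here too. Planned: 21 vs 14 facilities in 4 vs 4 LGs, so mean cluster size m = 5.25 and 3.5. Current: 16 vs 8 in 3 vs 4 LGs, so m = 5.33 and 2. The multiplier for 80% power is 1.960 + 0.842 = 2.802.

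**Display.** Per-arm design effect DEFF = 1 + [(1 + CV²)m − 1] × ICC, with 1 + CV² = 1.1369. SE = SD × √(DEFF₁/n₁ + DEFF₂/n₂). Power = Φ(18.8/SE − 1.96).

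- Planned: DEFF = 1.248 and 1.149. SE = 17.8 × √(1.248/21 + 1.149/14) = 6.70. Detectable difference 2.802 × 6.70 = 18.76. Power = Φ(2.808 − 1.96) = 80.2%. This reproduces the stated 18.8 and 80%.
- Current: DEFF = 1.253 and 1.064. SE = 17.8 × √(1.253/16 + 1.064/8) = 8.18. Detectable difference 2.802 × 8.18 = 22.9. Power = Φ(2.298 − 1.96) = 63.2%.

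**Sales.** Compare linear slopes over 156 weeks, with facilities as independent units and the difference taken at the end of the trial (155 × the weekly slope difference). The variance of one facility's slope follows from the AR(1) matrix. Under an independence working correlation, the SD of one facility's 3-year change is 9.27; under an AR(1) working correlation it is 9.08. SE = that SD × √(1/n₁ + 1/n₂). The square root is 0.345 as planned and 0.433 now.

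| | SE | Detectable difference (80%) | Power at 9 points |
|---|---|---|---|
| Planned, independence working | 3.20 | 9.0 | 80.4% |
| Planned, AR(1) working | 3.13 | 8.8 | 81.9% |
| Current, independence working | 4.01 | 11.2 | 61.2% |
| Current, AR(1) working | 3.93 | 11.0 | 62.9% |

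The planned rows reproduce the stated 9 points at 80%. As a check that needs no slope model, the SE ratio is √(0.1875/0.1190) = 1.255. Scaling exactly 80% power at 9 points by this ratio gives a detectable difference of 9 × 1.255 = 11.3 and power of 61%.

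**Sensitivity, display at current numbers.** Cluster sizes after attrition are not given, so CV 0.37 is an assumption. Varying CV from 0 to 0.8 moves power from 64% to 60%. An ICC of 0 gives 68%, and 0.10 gives 59%. None of these comes near 80%.

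**Small-cluster reference, display, like for like.** With a t distribution on number of LGs minus 2 degrees of freedom, power at 18.8 points is about 65% as planned (6 df) and about 46% now (5 df).

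**The case against.** The attrition is disclosed, with counts, in the same paragraph, and the section says that the calculation used the numbers recruited. The design arithmetic is correct. All of that stands: nothing is concealed or miscalculated. But disclosing the counts does not correct a claim about the power that the trial will have.

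The plan may also recover some precision. The section on statistical methods adjusts for facility characteristics, models the six-monthly audits over time and analyses all randomised participants with available data. December 2024 is an interim count in a trial that runs to July 2026. This stands too, and it is why the current figures are conditional. The article quantifies no such gain, lists none among the inputs to the 18.8-point figure, and does not say that withdrawn facilities supply data.

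Four stronger readings are tempting, and the document does not support them:

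- *Display power has fallen from 80% to 46%.* This compares a normal-based figure with a t-based one. The t reference already gives about 65% at the planned size, so about 15 of those 34 points come from the change of method.
- *Sales power is 58% or lower.* That needs an LG-level ICC, and the section states none for sales. If 0.05 is assumed, the design-stage baseline also drops, to about 75%.
- *These are the actual powers for the co-primary outcomes.* Those outcomes cover RED food and drink, with sales measured as volume. The SDs of 17.8 and 13.7 are stated only in the drinks calculations, so power for the full outcomes cannot be computed from the article.
- *The benchmark comparisons are false.* As statements about the design effect sizes they hold: 18.8 is close to 18.9, and 9 is below 11. They do not carry over to current numbers.

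**Conclusion.** The point holds. A power claim in the future tense rests on numbers that the same paragraph supersedes. On the plan's own inputs and the normal approximation that reproduces its 80%, attrition alone lowers power by about 17 points for RED drinks displayed and by about 19 points for RED drink sales. The detectable display difference is now about 4 points above the −18.9% benchmark. The sales figure has lost its 2-point margin and sits at or slightly above 11, so that crossing is slight.

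The result assumes unchanged SDs, ICC, CV and autocorrelation, independent facilities for sales, and no gain from covariates or repeated audits. The conclusion that power is well short of 80% does not depend on the exact CV or ICC for display.

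**What to change.** In Sample size considerations:

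1. Label the two 80% statements, and both comparisons with Water in Sport, as design-stage, based on 35 facilities in eight LGs.
2. After the December 2024 counts, add wording such as: With 16 and 8 facilities in three and four LGs, and the planning inputs unchanged, power is about 63% for a difference of 18.8 points in RED drinks displayed and about 61–63% for 9 points in weekly RED drink sales. The differences detectable with 80% power are about 23 and 11.0–11.3 points. Keep the word drinks, and state that CV 0.37 is assumed to persist.
3. Say that these detectable differences are no longer similar to 18.9 (display) or smaller than 11 (sales), and that a null result would not exclude effects of 18.8 or 9 points. A matching sentence belongs in the limitations.
4. If a small-cluster t reference is also reported for display, give both values: about 65% as planned and 46% now. Leave out sales figures with an added ICC, or give them with their own design-stage baseline and mark the ICC as an assumption.

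The cost is a few sentences. Design, conduct and analysis do not change, but the stated figures become less favourable.

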### Randomisation and blinding

Eight LGs were paired based on location (regional/urban), the socioeconomic index for areas,^37^ and the number of engaged facilities. At the end of September 2021, a statistician independent of the project produced the restricted random sequence to allocate LGs to Intervention or Control within pairs. The nature of the intervention precludes concealing LG allocation, as participants were informed of their grouping by the project lead. Data collectors, who are employees of the participating LGs, will not be blinded to intervention allocation. The study statistician will be blinded during analysis. After randomisation, one LG dropped out prior to the start of the trial in October 2022, citing altered LG capacity to participate.

### Data collection

Data collection will be conducted by project officers in Intervention LGs and nominated data collectors in Control LGs, who will receive annual training by the research team and HEAS to enhance the rigour of their data collection practices. The research team will also collect data independently at T0 and T6, to ensure objectivity of results for overall trial evaluation. This will also ensure that any final changes implemented within the intervention group, between T5 and trial end, will be captured.

#### Primary outcomes

##### Implementation

Facility photo audits will be conducted using a standardised protocol where photos of the whole outlet, along with detailed photos of each food and drinks section, promotional/advertising materials, menus and recipes, vending machines and all food and drinks stocked including nutrition panel will be captured every 6 months. For all pre-packaged products on display in each facility, photos will be used so that their healthiness can be ascertained. For products prepared onsite or where nutrition information is unknown, average nutrient content will be estimated using the Nutrition Panel Calculator by Food Standards Australia New Zealand^38^ or by matching each product to similar generic products within AUStralian Food and NUTrient Database (AUSNUT).^39^ All pre-packaged products, recipes for products prepared onsite and relevant nutrition information from photo audits will be entered into the FoodChecker web software^35^ which classifies each product as ‘GREEN’, ‘AMBER’ or ‘RED’ according to the Guidelines and determines the percentage of food and drinks on display in each of these three categories in each facility. FoodChecker assessments will be completed by project officers in the Intervention Group and by the research team for the Control group. At least 10% of the Intervention and Control group FoodChecker assessments will be cross-checked by the research team at T0 and T6.

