#### Human resource support

The key component of the Promoting CHANGE support package involves salary support for skilled LG project officers trained in health promotion and/or facility management to deliver tailored, localised facilitation strategies.^33^ Project officer salary support was budgeted as half a day per week per LG for administrative tasks, evaluation, policy development, training and other capacity-building exercises, along with an additional half a day per facility for delivering tailored support to the sports and recreation facility food outlet. Examples of healthy choices implementation support include choosing specific new products based on supplier availability in the LG area and food preparation facilities within the outlet; marketing strategies tailored to customer base, for example, school carnivals for outdoor pools, demography of patrons. Of this, LGs agreed to fund 1 day worth of salary support and all staff on-costs; the NHMRC grant will fund the remainder of staff time. During the third year of the trial, grant-supplied salary support will be reduced by half as the project moves towards a long-term maintenance phase as indicated in figure 2.

LG project officers will collaborate with facility staff and management to advance implementation of the Guidelines. This includes creating or modifying recipes, identifying healthier product options and suppliers, training facility staff in improving the healthiness of the food outlet, creating communication and promotional materials and conducting six monthly in-store audits and collecting sales data. Decisions regarding which aspects of the Guidelines to prioritise will be made jointly by LGs and facilities with guidance from the Australian National Nutrition Foundation’s Healthy Eating Advisory Service (HEAS). LGs will be encouraged to draft policies aimed at embedding long-term changes, such as lease agreements and mandating compliance with the Guidelines.

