#### Primary outcomes

Implementation: At each facility, percentage of least healthiest ‘RED’ food and drink products available will be estimated from the products on display at the time of the audit. Effectiveness: At each facility, percentage of least healthiest ‘RED’ food and drink product volume (kg or L) purchased per week will be calculated using weekly sales data.

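### The FoodChecker assessor differs by arm for the display co-primary outcome, and the protocol does not say that the research team's T0 and T6 data replace the project officers' classification

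*Protocol article*

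**What the plan says.** The implementation co-primary outcome is the percentage of RED items at each facility. Under Primary outcomes, RED "food and drink products available will be estimated from the products on display at the time of the audit". The Implementation part of Data collection describes photo audits every six months, with product and recipe information entered into FoodChecker, which assigns the colour and returns the percentages. The same part divides that work by arm: "FoodChecker assessments will be completed by project officers in the Intervention Group and by the research team for the Control group".

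Other sections bear on this:

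- Human resource support: "LG project officers will collaborate with facility staff and management to advance implementation of the Guidelines". The officers' tasks include changing recipes, finding healthier products and conducting the audits.
- Randomisation and blinding: "Data collectors, who are employees of the participating LGs, will not be blinded to intervention allocation". Only the study statistician is blinded.
- Data collection, on who takes the routine audit data: "Data collection will be conducted by project officers in Intervention LGs and nominated data collectors in Control LGs".
- Implementation, for on-site products or those with unknown nutrition information: "average nutrient content will be estimated using the Nutrition Panel Calculator by Food Standards Australia New Zealand", or the product is matched to a similar generic one in a food composition database.

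There are two safeguards. Data collection states: "The research team will also collect data independently at T0 and T6, to ensure objectivity of results for overall trial evaluation". Implementation states: "At least 10% of the Intervention and Control group FoodChecker assessments will be cross-checked by the research team at T0 and T6".

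**The concern.** Every Intervention facility is assessed by one kind of assessor and every Control facility by another. The Intervention assessors know the allocation and are working to lower the quantity that they measure. Under Capability enhancement, guidance on classifying products with FoodChecker is itself part of the support package, so their practice may differ from the research team's for that reason too.

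A systematic difference between the two groups in which items are entered, or in how nutrients are estimated for unlabelled items, would appear in the comparison as an effect of the intervention. Blinding the statistician does not help, because the difference would already be in the data. At stake is the validity of one of the two co-primary comparisons at 3 years, and of the over-time analysis that uses the six-monthly audits.

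**Working it through.** **1. Does the split apply at the primary timepoint?** Statistical methods assesses the display outcome first at the 3-year mark, then over the six-monthly audits. The sentence that divides FoodChecker work by arm makes no exception for T0 or T6. The next sentence has the research team cross-check a share of Intervention assessments at T0 and T6, which implies that officers' assessments exist at those timepoints. The statement on independent T0 and T6 collection concerns gathering data. It does not say who runs FoodChecker on those data, or that the result replaces the officers' result.

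**2. How much does the cross-check cover at its minimum?** Sample size considerations gives 16 Intervention and 8 Control facilities as of December 2024. Assuming one assessment per facility per timepoint:

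- Intervention: 0.10 × 16 = 1.6, so about 2 of 16.
- Control: 0.10 × 8 = 0.8, so about 1 of 8. Here the research team checks its own work.

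The 10% is a floor, so actual coverage may be higher. No cross-check is stated for T1 to T5.

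**3. Reproducing the plan's own figure, to obtain a standard error.** Inputs from Sample size considerations: ICC 0.05, coefficient of variation of cluster size 0.37, SD 17.8, two-sided α 0.05, power 80%, and 21 facilities in four LGs against 14 in four LGs.

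- Design effect per arm: DEFF = 1 + ((CV² + 1)m − 1) × ICC, with m the mean number of facilities per LG.
- Intervention, m = 21/4 = 5.25: DEFF = 1.248. Control, m = 14/4 = 3.5: DEFF = 1.149.
- SE = 17.8 × √(1.248/21 + 1.149/14) = 6.70.
- Detectable difference = (1.960 + 0.842) × 6.70 = 18.76 points. With the rounded cluster sizes of 5 and 4 it is 18.85.

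The stated 18.8 points is reproduced and is not in dispute.

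For the December 2024 numbers (16 in three LGs, m = 5.33; 8 in four LGs, m = 2): SE = 17.8 × √(1.253/16 + 1.064/8) = 8.18.

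**4. Illustration of a differential.** Let b be the points by which RED is under-recorded in the Intervention arm relative to Control, with no true effect. The documents give no value for b, so the range is assumed. The two-sided rejection probability is Φ(−1.96 − b/SE) + 1 − Φ(1.96 − b/SE).

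| b (assumed) | Planned facilities, SE 6.70 | December 2024 facilities, SE 8.18 |
|---|---|---|
| 0 | 5.0% | 5.0% |
| 2 | 6.0% | 5.7% |
| 5 | 11.6% | 9.4% |
| 10 | 32.1% | 23.1% |

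For scale, if true RED were 40% (also assumed), b = 5 would need 5/40 = 12.5% of RED items to be recorded as non-RED in one arm only, and b = 10 would need 25%.

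Two limits apply. The SD of 17.8 is given for RED drinks, whereas the outcome covers food and drinks. The normal approximation is also generous with seven or eight LGs. The table shows sensitivity and is not a forecast.

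**The case against.** The strongest reply is that the endpoint is already protected. The research team gathers its own data at T0 and T6 for the stated purpose of objectivity, and a natural reading is that these data serve the 3-year evaluation. FoodChecker is rule-based and packaged products are photographed with their nutrition panels, so discretion is narrow for them and named tools govern the rest. Routine photo capture is done by trained LG-based collectors in both arms. A condensed article may simply not spell out which data set is primary.

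Much of this stands, and it limits what may be concluded. A reader might infer more in four ways:

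- That bias is built into the outcome. The documents show a structural risk. Under-recording of RED by delivery staff is the plausible direction, but neither direction nor size can be derived.
- That an assessor effect could never be separated from the intervention effect. Photos, independent T0 and T6 data and the cross-check would allow disagreement to be estimated and items to be re-coded.
- That the bias would consume a given share of the 18.8-point target. That target is for drinks only, and any such share would rest on an assumed misclassification rate.
- That photo capture is also divided between officers and central staff. The division between officers and research team concerns FoodChecker entry.

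The objection does not dispose of the point itself. The protocol states an explicit rule tying assessor to arm and never says it is set aside at T0 and T6. Following the text as written would produce the confounded comparison.

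**Conclusion.** The concern holds as a risk of differential assessment. FoodChecker assessor is confounded with arm for the display co-primary outcome, and the Intervention assessors are unblinded and deliver the intervention. The T0 and T6 provisions mitigate the risk at the 3-year endpoint without removing it. T1 to T5, which feed the over-time analysis, have no stated check.

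The size is unknown. On the assumption of a 5-point differential and no true effect, two-sided type I error rises from 5% to about 9-12%, depending on whether current or planned facility numbers are used. This relies on the drinks-based SD and a normal approximation. Severity: should fix. The existing safeguards and the rule-based software do not support a finding that the outcome is already compromised.

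**What to change.** Amend the Data collection section and its Implementation part to state that:

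- the primary 3-year display analysis uses the research team's T0 and T6 data;
- the research team runs FoodChecker in the same way for all facilities in both arms, with LG and facility labels removed from the files where feasible;
- project officers' assessments are kept for feedback and for T1 to T5;
- agreement between officers' and research-team results at T0 and T6 is reported, and the over-time analysis is interpreted in its light.

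The cost is about 16 extra assessments at each of T0 and T6, on the December 2024 count and one assessment per facility. The team concerned already assesses Control and already collects data at both timepoints. The documents do not give the staff time per assessment. Study design reports year 2 of 3 complete, so T6 can be settled in advance, while T0 means re-coding data already collected. Masking will be imperfect, since photos may reveal the facility or its promotions.
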